### Study number and sample size

For prognostic information and estimated sufficient numbers of patients and events, we expect to recruit about 150 patients per year. With an expected 35–45 % recurrence rate within 5 years of primary diagnosis—which is expected from previous regional and national data of curatively resected CRC in Norway [2, 40, 43]—and, an accrual commencing over at least 5 years (2013–2018) we expect to have about 750 patients with operable primary and/or metastatic CRC for evaluation at the end of the period. In stage I-III CRC, the recurrence rate at 35–45 % by 5 years [2, 40, 43] should yield appropriate number of events (cancer-specific survival) for creation of test-sets, validation-sets and prospective evaluation. Recurrence rates are expected to be even higher in colorectal liver metastasis (>80 % recurrence within 5 years), suggesting fewer patients are needed to evaluate the endpoint.

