### Statistical analysis and endpoints

The project is exploratory and thus no formal statistical power has been done. The population-based, observational, real-life, non-selected cohort will allow for adequate power based on the expected recruitment of a cohort size of 750 patients, of which an expected one-third (about 250) will have recurrence or death from disease. With the high number of events, this will allow for reasonable multivariable adjustments for outcomes. For smaller samples in subgroups (e.g. only stage II; or, only patients with resected liver metastasis), hypothesis-generating results will be pursued with appropriate sized prospective cohort samples with internal and external validation cohorts, where available.

The main endpoints will be cancer-specific, recurrence-free and overall survival, which will be analysed with Kaplan–Meier figures and log rank test. Exploratory analyses will be done using descriptive techniques for hypothesis-generating results. For laboratory values without established cut-offs, we will apply receiving-operator characteristics (ROC) analyses for optimal cut-off determination [55]. For prognostic factors, we will apply appropriate multivariable regression analyses for appropriately adjusted analyses.

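### ROC-optimised cut-offs are not tied to the planned test and validation sets; set and tested in the same patients, they give false-positive rates of about 21–44% at an assumed nominal 5%

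*Protocol article*

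**What the plan says.** Under Statistical analysis and endpoints, the Protocol article names cancer-specific, recurrence-free and overall survival as the main endpoints, "which will be analysed with Kaplan–Meier figures and log rank test". The same paragraph then gives a rule for dichotomising laboratory values that lack an established threshold: "we will apply receiving-operator characteristics (ROC) analyses for optimal cut-off determination". It does not give the outcome against which the ROC curve is drawn, the time horizon, the criterion of optimality or any adjustment of the later test. Multivariable regression is added for prognostic factors.

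Validation appears in two relevant places:
- Study number and sample size: the expected recurrences in stage I–III disease are said to suffice "for creation of test-sets, validation-sets and prospective evaluation".
- Statistical analysis and endpoints: smaller subgroups are to be pursued "with internal and external validation cohorts, where available".

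Neither place mentions the ROC cut-offs.

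The article also says "The project is exploratory and thus no formal statistical power has been done". Positivity for circulating tumour cells is defined separately, from background levels in healthy controls (Circulating tumour cell (CTC) detection).

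**The concern.** Kaplan–Meier curves and log-rank tests need groups, and for a continuous marker without an accepted threshold the ROC rule supplies them. In a prognostic study whose main endpoints are all survival times, the natural reading is that the cut-off is chosen to separate patients with an event from those without. The log-rank statistic then compares groups that were picked to differ. Its usual reference distribution no longer applies, and both the p-value and the hazard ratio are biased towards an effect.

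The project intends to examine many candidate markers, and its Discussion blames earlier research for promising markers that were never validated. An analysis rule that passes a large share of null markers would add to that problem.

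**Working it through.** **The article's own figures.** "we expect to recruit about 150 patients per year" over five years gives 150 × 5 = 750. The analysis section expects a "cohort size of 750 patients, of which an expected one-third (about 250) will have recurrence or death from disease", and 750 / 3 = 250. Both reproduce.

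**Assumptions the article does not supply.** Two-sided nominal level 5%; ROC against event status; cut-off at the maximum of J = sensitivity + specificity − 1 (Youden); a marker unrelated to outcome.

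**Simulation.** Event times are exponential with rate λ = −ln(1 − p)/5, where p is the proportion with an event by 5 years; for p = 1/3, λ = 0.4055/5 = 0.081 per year. Follow-up stops at 5 years. The marker is cut at its Youden point and the groups are compared by log-rank (rejected if U²/V > 3.84). There were 4,000 runs per setting. The Monte Carlo standard error is √(0.42 × 0.58/4000) = 0.8 percentage points near 42% and √(0.05 × 0.95/4000) = 0.3 near 5%.

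| Setting | False-positive rate | Multiple of 5% |
|---|---|---|
| 750 patients, one-third events, direction free | 40.5–42.1% | 8.1–8.4 |
| Same, direction fixed in advance | 21.1–25.3% | 4.2–5.1 |
| 750, 40% events (0.40 × 750 = 300), direction free | 39.0% | 7.8 |
| 150, one-third events, direction free | 37.1–39.4% | 7.4–7.9 |
| 100, 80% events, direction free | 30.6–31.1% | 6.1–6.2 |
| 750, cut-off set in 375, tested in the other 375 | 5.4% | 1.1 |

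Ranges within a row come from leaving the cut-off unrestricted or excluding the extreme tails of the marker. Separate sets of simulations of the first row gave 39–44%, and another run of the split-sample row gave 4.9%. The 40% event rate lies in the middle of the article's 35–45% recurrence figure. The 80% setting reflects its figure for liver metastases; the subgroup size of 100 is an assumption.

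**Checks.**
- Cutting at the median instead gave 4.3–5.5% at 750 patients, so the test itself is sound and the optimising causes the excess.
- The Miller–Siegmund approximation for a maximally selected test is φ(z)(z − 1/z) ln[(1 − ε)²/ε²] + 4φ(z)/z. With z = 1.96, φ(z) = 0.0584 and ε = 0.10 it gives 0.0584 × 1.450 × 4.394 + 4 × 0.0584/1.96 = 0.372 + 0.119 = 0.49. With ε = 0.20 it gives 0.235 + 0.119 = 0.35. The order of magnitude agrees.
- Adding random censoring at 750 patients gave 39.2–41.6%, and staggered censoring with a 40% event rate gave 37.4%. Censoring does not drive the inflation.

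**Hazard ratio.** With direction free at 750 patients, the median spurious hazard ratio, always expressed above 1, was about 1.3. Some of that is chance. For an unoptimised even split with 250 events, the standard error of log HR is about 2/√250 = 0.126, and the corresponding median is exp(0.674 × 0.126) = 1.09. The rest comes from choosing the cut.

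**The case against.** The article is a condensed, openly exploratory protocol. It states no significance level, no confirmatory test and no power calculation. It does not write that the ROC is run against survival status, nor that the resulting groups are tested in the same patients. It plans test and validation sets, aims to follow REMARK for prognostic work, and adds multivariable regression. If those sets were used for the cut-offs, the inflation would disappear.

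Much of this stands, and it rules out three stronger readings that a reader might infer:
- *The plan builds in an eightfold error rate.* Eightfold needs an assumed 5% level, a free direction and reuse of the same patients.
- *Validation is foreseen only for small subgroups.* The sample-size section foresees it for stage I–III disease, the main population.
- *The analysis ignores censoring.* The article is silent on whether the ROC is time-dependent, describes loss to follow-up as minimal and sets outcomes at five years. Some concern remains: recruitment closes in 2018 and five-year follow-up ends in 2022, so with even accrual over 2013–2018 between none and 1/6 (about 17%) of patients could have less than five years. Deaths from other causes add to this.

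What does not stand is that the sets or the label resolve the matter. The ROC rule is a stated method rather than a detail left out. No sentence assigns the derivation of cut-offs to one set and their testing to another, and multivariable adjustment does not undo an optimised cut.

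**Conclusion.** The point holds in a conditional form. The article prescribes outcome-optimised dichotomisation (on its natural reading) and log-rank testing, with neither separation of samples nor correction. If the same patients serve both purposes, the false-positive rate at an assumed 5% is about 21–44% at 750 patients and about 250 events: four- to fivefold with the marker's direction fixed, about eightfold with it free, and about sixfold in a small subgroup with 80% events. Testing in separate patients brings it to about 5%.

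The exploratory label lowers the stakes but does not make such p-values or hazard ratios valid. The point is confined to laboratory values without established cut-offs; circulating tumour cell positivity is outside it.

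**What to change.** Amend the ROC sentence under Statistical analysis and endpoints along these lines: *Any ROC-derived cut-off is determined only in the training set (the test set named under Study number and sample size), against event status at a stated horizon, using a method that allows for censoring. Its p-value and hazard ratio are reported only from the validation set, or with a correction for maximally selected statistics or by bootstrap that repeats the choice of cut-off in each resample.* The article should also say which of its sets is used for derivation, since the term test set is ambiguous.

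Analysing the marker as continuous in the regression models is an acceptable alternative and avoids the problem; it is a choice, not a requirement.

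The cost is modest extra programming, some loss of precision if the cohort is split, and some markers that will look less impressive. No new data are needed, provided the change is made before the markers concerned are analysed.

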## Discussion

The ACROBATICC projects aim to integrate the routine clinical work-up and treatment of patients with primary CRC and resectable liver metastasis with state-of-the-art molecular technology investigations of blood samples and tumor tissues. The aim is to explore and identify better predictive and prognostic biomarkers that may eventually help in clinical decision-making for more precise, personalized and tailored treatment. The ACROBATICC clinical and molecular biobank repository will serve as a long-term source for novel exploratory analysis and invite collaborators for mutual validation of promising biomarker results. The project aims to generate results that can help better discern prognostic groups in stage II/III cancers; explore prognostic and predictive biomarkers, and help detail the biology of colorectal liver metastasis for better patient selection and tailored treatment [23, 28, 56].

The role of population-based cancer biobanking is increasingly recognized as important for exploratory and confirmatory studies at an unselected, population-level. While regular diagnostic biobanking [i.e. formalin-fixed and paraffin embedded (FFPE) tissue blocks] allow for valuable analyses outside routine descriptive data, such repositories may have a number of medicolegal and laboratory limitations which may be overcome by specific research-driven projects. The current translational cancer research project will allow for further in-depth analyses into cancer biology otherwise not available from material obtained by routine care.

The use of “liquid biopsy” has gained considerable attention as a novel source of biomarkers. Blood-based biomarkers could prove to be practical tools for CRC detection, as the monitoring of biomarkers in biological fluids offers many advantages, including minimal invasiveness and easy accessibility [57]. In the current study, we will have the opportunity to explore for tumour-specific markers in blood and tissue that may be related to prediction and prognosis of outcome.

Lack of uniform research designs, poor quality control and large variation in reporting have hampered biomarker research and comparison of data in the past. This has invariably led to a number of promising but non-validated biomarkers in past studies. Currently, a large number of guidelines and recommendations are available to instruct, inform and impede better and more uniform reporting of results. However, the number of such guidelines is increasing rapidly [58], with some suggesting there be too many guidelines to possibly comply to. However, we believe that a core set of important guides help set useful framework for reporting and help avoid huge deviation from recommended practice. Evaluation of compliance to such guidelines suggest that considerable deviation and lack of reporting core data still exist in biomarker research studies [59]. Thus, we would seek to adhere and comply with the recommendations addressed in the protocol and any other relevant recommendations, as issued by the EQUATOR network (http://www.equator-network.org).

### Project status

The project is currently recruiting patients and laboratory work on the CTCs is ongoing, as well as laboratory work on MSI and EMAST in primary tumours. Hot spot panels of known CRC mutations with NGS technology is being prepared. A pilot, feasibility study to test for same-time comparison of patients’ circulating immune-cells in peripheral blood and comparison to tumour-infiltrating cells in the cancer specimen is currently being conducted.

### Future aspects

We envision several add-ons to be possible with increases resources and manpower in the project. For one, patient reported outcomes (PROs) is an increasing are of interest and would yield yet another dimension to the clinical-translational aspect of the project [60]. Also, the sampled biopsies will allow for a number of other experiments and analyses, such as exosomic DNA, microRNA and other emerging biomarkers. Further, other sampling techniques and specimens would be feasible in the future, such as sampling and investigating faeces for both genetic and epigenetic biomarkers [24], but also investigating the microbiome for its putative role in carcinogenesis but also possible influence on cancer biology [61, 62]. Last, but not least, we would pursue international collaboration for mutual validation of similar ongoing biomarker projects [63]. The prospective cohort results will seek collaboration for external validation studies but may also serve as an external validation cohort for other research groups interested in collaboration.

## Abbreviations

CRC: colorectal cancer
CLM: colorectal liver metastasis
CTC: circulating tumour cell
NGS: next-generation sequencing
EMAST: elevated microsatellite alterations in selected tetranucleotides
MSI: microsatellite instability
IHC: immunohistochemistry
TNM: tumour-node-metastasis
CIMP: CpG-island methylator phenotype
CIN: chromosomal instability
SUH: Stavanger University Hospital
NGICG: Norwegian Gastrointestinal Cancer Group
FFPE: formalin-fixed paraffin-embedded
GWEF: glacial acetic acid, water, ethanol, formalin
ROC: receiving-operator characteristics
H&E: haematoxylin and eosin
PROs: patient reported outcomes
